## Methods and design

### Study design

The study is a prospective two years parallel group, examiner-blinded, randomized controlled trial with an intelligent physical exercise training (IPET) intervention group and a control group (CG) conducted in accordance with the CONSORT statement [29]. The enrollment was sequential in 6 strata from May 2011 to March 2012 and with baseline as well as one and two year follow-up measures. All participants gave their written informed consent to participate. The local Ethics Committee of Southern Denmark approved the study protocol (S-20110051), which qualified for registration in ClinicalTrials.gov (NCT01366950). Employees were assigned an arbitrary ID number, which was concealed by an authorized technical staff person. The IDs were randomized individually within each strata following baseline measures using a random number computer algorithm and balanced for gender in strata with less than 100 employees. All test personnel and investigators involved in data treatment were blinded to the randomization.

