#### Self-reported measures

##### Questionnaire

All employees completed a questionnaire three times: at baseline as well as after one and two years of intervention. Questions addressed: demographics, education, job, income before tax, productivity [26], workability [27], psychosocial aspects [47], pain/kinesiophobia, self-rated health [48], sick leave, smoking, alcohol, physical activity at leisure [49], and sports activities specified as: ball games, Nordic walking, jogging, cycling, aerobics, spinning, dancing, swimming, kayaking/rowing. Questions regarding musculoskeletal disorders were assessed by a modified version of the Nordic questionnaire of musculoskeletal disorders [50]. Cut points for recommending strength training for neck/shoulder or functional training for core stability were > 30 days complaints during the last year in the neck/shoulder area and low back area, respectively. At follow-up after one and two years, respectively, questions regarding adherence as well as the impact of the health ambassadors were included. Their impact was rated from 1 for no impact to 10 for major impact.

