### Statistics

All results are reported as mean (SD) and p < 0.05 is considered statistically significant. Primary and secondary outcomes will be analyzed within (paired t-test) and between the intervention group and the control group after intervention (ANCOVA). Categorical variables will be tested using chi-square and McNemar tests. Analyses will be performed using SPSS statistical software, version 21. Intention to treat analyses will be performed and values carried forward and backwards for missing values in both baseline and follow up measurements. If measurements have missing values in both baseline and follow up they will be replaced by means of all existing data in each group, respectively. Per-protocol analysis will be carried out with employees from the training group who meet the criteria of at least 70% adherence in the training period [51]. Sample size calculation is based on a 5% improvement in VO_2max_ on a group level with a SD of 20%, type 1 error of 5% and a power of 80% which showed a requirement of 128 employees in each group [52]. With an estimated dropout of 30% the research project has to recruit around 400 employees.

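### The plan fixes an unadjusted chi-square as the only between-arm test for categorical variables, leaving out baseline status and company strata: valid, but less efficient than it need be

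*Protocol article*

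**What the plan says.** - **Tests (Statistics).** Primary and secondary outcomes are analysed within arms by paired t-test and "between the intervention group and the control group after intervention (ANCOVA"). The next sentence deals with categorical data: "Categorical variables will be tested using chi-square and McNemar tests". Read together, ANCOVA serves the continuous outcomes, and chi-square and McNemar serve the categorical ones. The covariates of the ANCOVA are not listed.
- **Randomisation (Study design).** "The enrollment was sequential in 6 strata from May 2011 to March 2012", each stratum being a company. "The IDs were randomized individually within each strata following baseline measures", and allocation was "balanced for gender in strata with less than 100 employees".
- **Baseline data (Questionnaire).** "All employees completed a questionnaire three times: at baseline as well as after one and two years of intervention". Under Procedure, completing the questionnaire was a condition of joining, so baseline answers exist for all participants by design.
- **Where it could matter.** Hypothesis 2 includes a decrease in musculoskeletal disorders, which are assessed with a modified Nordic questionnaire.

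**The concern.** The article does more than leave the categorical analysis open: it names the test. A chi-square on the arm-by-outcome table at follow-up has no place for a covariate. McNemar uses the baseline/follow-up pair, but only to ask whether one arm changed, and two such answers do not make a randomised comparison. Two kinds of information already in hand therefore stay out of the treatment comparison: each participant's own baseline status, and the company within which that participant was randomised.

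What is at stake is efficiency. The sample size was set on VO2max, so no power target protects a categorical outcome. A null result for complaints could then partly reflect the choice of test. The section is also uneven, since continuous outcomes get a covariate-capable method and categorical outcomes do not.

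**Working it through.** **No figure in the plan to reproduce.** The article gives no rate, effect or power for any categorical outcome. Its one sample-size figure (128 per group) is for VO2max and does not enter here.

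**What each named test can use**

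| Test | Compares arms? | Uses own baseline? | Uses company? |
|---|---|---|---|
| Chi-square | yes | no | no |
| McNemar | no (within arm) | yes | no |
| ANCOVA (continuous outcomes) | yes | possible; covariates not listed | possible; covariates not listed |

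**Illustrative simulation.** From the documents: about 400 participants, six strata, individual randomisation within stratum, gender balanced in strata below 100. Assumed: stratum sizes 100, 80, 70, 60, 50 and 40 (sum 400), 1:1 allocation, 60% of one gender, complete follow-up, and

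logit P(outcome) = company + 0.5(gender − 0.5) + β(baseline − 0.5) + δ·arm

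Baseline status is generated from the same company and gender terms. Company terms are all 0 (none), −0.6 to 0.6 (moderate) or −1.2 to 1.2 (large). β = 0 means no baseline link; β = 2 is a strong one. δ = 0 for the null (3,000 runs) and 0.6 for power (1,500 runs).

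Statistics compared, two-sided 5%:

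- Chi-square: z = (p1 − p0) / √[p(1 − p)(1/n1 + 1/n0)].
- Cochran-Mantel-Haenszel (CMH): z = Σ(a − n1·m1/N) / √Σ[n1·n0·m1·m0 / (N²(N − 1))], summed over company × gender cells, and then over company × gender × baseline cells. Within a cell, a is the number of events in the intervention arm, n1 and n0 the arm sizes, m1 and m0 the numbers with and without the event, and N the total.

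Rejection rates (%), in the order chi-square / CMH by company × gender / CMH adding baseline:

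| Company differences | β | Null | Power |
|---|---|---|---|
| none | 0 | 5.2 / 5.2 / 5.0 | 83.3 / 83.7 / 83.3 |
| none | 2 | 5.6 / 5.6 / 5.6 | 64.1 / 64.9 / 72.5 |
| moderate | 0 | 4.9 / 5.2 / 5.5 | 81.9 / 83.3 / 80.9 |
| moderate | 2 | 3.9 / 4.3 / 4.7 | 61.5 / 64.3 / 72.7 |
| large | 0 | 3.5 / 4.9 / 5.0 | 74.7 / 79.4 / 77.4 |
| large | 2 | 2.5 / 4.8 / 5.2 | 53.2 / 60.8 / 66.3 |

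Simulation error: √(0.05 × 0.95 / 3000) = 0.4 points for the null, and √(0.65 × 0.35 / 1500) = 1.2 points for a power near 65%.

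**Reading the table**

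1. Validity: chi-square rejects 2.5% to 5.6% under the null. The 5.6% is within 1.5 simulation errors of 5%. The 2.5% is clearly below it: balanced allocation removes company variation from the arm difference, but the pooled variance still counts it.
2. Strata: CMH by company × gender gains between 83.7 − 83.3 = 0.4 and 60.8 − 53.2 = 7.6 points over chi-square.
3. Strata plus baseline, strong link: 72.5 − 64.1 = 8.4, 72.7 − 61.5 = 11.2 and 66.3 − 53.2 = 13.1 points over chi-square.
4. Baseline without a link: adding it to the stratified test changes power by 83.3 − 83.7 = −0.4, 80.9 − 83.3 = −2.4 and 77.4 − 79.4 = −2.0 points.

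**The case against.** The strongest reply is that this is a preference about efficiency for variables that are not primary, analysed with a valid test. The sentence speaks of categorical variables, which may include descriptors such as smoking or education. Nowhere does the article say that complaints will be dichotomised and compared by chi-square; the cut at more than 30 days is a rule for recommending training, not an outcome definition. All of this stands, and it is why the point is conditional on a categorical outcome being compared between arms. It does not remove the point: for any such outcome the article fixes the test, so an analysis plan would have to replace that test, not merely fill in detail.

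A reader might infer more than the text supports:

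- **That the whole analysis ignores company and gender.** The ANCOVA covariates are unlisted in a condensed article. Silence neither includes nor excludes them.
- **That error bars are misstated, or false positives inflated.** Results are reported as mean (SD), and no error bar or interval is defined. The chi-square was nominal to conservative.
- **That gender imbalance in the larger strata biases results.** Chance imbalance under randomisation is covered by the type 1 error. Stratum sizes are not shown either; with almost 400 enrolled in six strata, at most three could reach 100.
- **That adjustment shrinks the standard error by a fixed share.** An assumed baseline correlation of 0.4 to 0.6 suggests 16% to 36% less variance (r²), but that is linear-model arithmetic. In logistic regression a predictive covariate raises the standard error of the log odds ratio. The gain comes because the conditional effect grows more, and it appears as power.

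**Conclusion.** The point holds as a low-cost improvement, not as an error that threatens the trial. As written, a categorical outcome compared between arms would be tested without baseline status or randomisation strata, although both are available. The chi-square test is valid, and it turns conservative if companies differ.

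The size is illustrative only. Using company, gender and baseline together gained about 8 to 13 power points under an assumed strong baseline link, with up to 7.6 of those from company and gender alone. With no link, baseline adds nothing and any gain is limited to the strata. These figures assume the stratum sizes, company differences and effect given above, and complete data on 400 participants. The simulation used CMH tests, so it shows the order of gain to expect from logistic regression, not its exact value. The primary analysis of VO2max is untouched.

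**What to change.** In the Statistics section, keep chi-square for descriptive tables, and replace it for between-arm comparisons of categorical outcomes with one of the following:

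- **Preferred:** logistic regression, or modified Poisson if a risk ratio is wanted, with arm, baseline status, company (six levels) and gender. Report the adjusted effect with its 95% CI. An adjusted odds ratio is conditional on the covariates and should not be read against a crude one.
- **Minimum:** a Cochran-Mantel-Haenszel test stratified by company, with the stratified effect estimate and its 95% CI.

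State that McNemar results describe change within an arm and are not evidence of a treatment effect. For a binary outcome the preferred model has eight coefficients besides the intercept (arm 1, baseline 1, company 5, gender 1). That is manageable with around 400 participants unless the outcome is rare, in which case the stratified test is the fallback.

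The cost is a change of wording. No new data, visits or participants are needed. The choice should be fixed before the arms are compared.

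### The stated inputs do not give 128 per group for the between-group comparison; 128 matches a one-sample or paired t-test, and the 80% power holds for the randomised comparison only under an unstated baseline correlation

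*Protocol article*

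**What the plan says.** The Study design section describes a two-arm parallel randomised trial, exercise training against control. The Outcome measures section names estimated VO2max as the primary outcome.

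The Statistics section gives the sample-size basis: "Sample size calculation is based on a 5% improvement in VO_2max_ on a group level", with an SD of 20%, and "type 1 error of 5% and a power of 80% which showed a requirement of 128 employees in each group". It continues: "With an estimated dropout of 30% the research project has to recruit around 400 employees".

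The same section plans paired t-tests within each group and a comparison "between the intervention group and the control group after intervention (ANCOVA". It sets the significance threshold as "p < 0.05 is considered statistically significant". It does not say whether the test is one- or two-sided, whether the SD is that of VO2max or of its change, what correlation between baseline and follow-up is assumed, which formula was used, or which covariates enter the ANCOVA.

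**The concern.** The section gives an effect, an SD, an error rate, a power and a resulting number per group, so the number can be checked. It is about half of what the same inputs give for two independent groups.

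A within-group test asks whether VO2max changed in one arm and makes no use of the control group. If the 80% belongs to that test, it does not describe the randomised comparison of the primary outcome. A null between-group result could then be read as adequate evidence against a 5% effect when the trial may not have had that power.

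**Working it through.** **Inputs** (Statistics section): difference 5%, SD 20%, so d = 5/20 = 0.25; type 1 error 5%; power 80%; 128 per group; about 400 recruited with 30% dropout. Two-sided testing is assumed, and one-sided is also tried. Powers below are t-based; the normal approximation differs by at most about one percentage point.

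**1. Reproducing 128.** One-sample or paired test: n = [(1.960 + 0.842) × 20/5]² = 125.6. With the t correction this is 127.5, which rounds up to 128, an exact match.

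**2. Two independent groups, unadjusted.** n per group = 2 × 125.6 = 251.2; t-based 252.1, so about 252. One-sided: 2 × [(1.645 + 0.842) × 20/5]² = 197.8; t-based 198.5, so 199. Sidedness does not explain 128.

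**3. The dropout step.** 2 × 128 = 256 and 256/0.7 = 366, which about 400 covers. That step is sound. Evaluable per group: 400 × 0.7/2 = 140.

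**4. Unadjusted two-sided power for a 5% difference.** The non-centrality is 0.25 × √(n/2). The difference detectable with 80% power is about 2.802 × 20 × √(2/n).

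| n per group | non-centrality | power | detectable difference |
|---|---|---|---|
| 128 | 2.00 | 51% | 7.0% |
| 140 | 2.09 | 55% | 6.7% |
| 200 (no loss) | 2.50 | 70% | 5.6% |

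**5. ANCOVA adjusted for baseline.** The correlation r is not in the document, so r = 0.5 to 0.8 is an assumed range. Equal variances at the two times are also assumed.

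- If 20% is the cross-sectional SD, the residual SD is 20 × √(1 − r²).
- If 20% is the SD of change, the variance of change is 2σ²(1 − r) and the ANCOVA residual variance is σ²(1 − r²). The residual SD is therefore 20 × √[(1 + r)/2].

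| r | residual SD, cross-sectional | power at 128 / 140 / 200 | residual SD, SD of change | power at 128 / 140 / 200 |
|---|---|---|---|---|
| 0.5 | 17.3 | 63 / 67 / 82% | 17.3 | 63 / 67 / 82% |
| 0.6 | 16.0 | 70 / 74 / 88% | 17.9 | 61 / 64 / 80% |
| 0.7 | 14.3 | 80 / 83 / 94% | 18.4 | 58 / 62 / 77% |
| 0.8 | 12.0 | 91 / 94 / 99% | 19.0 | 56 / 59 / 75% |

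**6. What would make 128 right for the randomised comparison.** With a cross-sectional SD: 251.2 × (1 − r²) = 128 gives r = √(1 − 128/251.2) = 0.70. With an SD of change: (1 + r)/2 = 128/251.2 gives r = 0.02, which means almost no correlation between a person's two measurements.

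**The case against.** **The planned analysis is ANCOVA, not an unadjusted t-test.** This stands, and it limits the claim. A reader might infer from step 4 that the trial has only 51–55% power. The document does not support that as the power of its own analysis, because baseline adjustment would raise it. Nor does power stay at 55% if 20% is the SD of change; at 140 per group it is 59–67% over the assumed range of r.

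**The origin of 128 is not stated.** This also stands. A reader might infer that a paired formula was certainly used. The exact match and the planned paired t-tests point that way. But ANCOVA with a cross-sectional SD and r = 0.70 also gives 128.1 by the normal formula, and the section cites a source that is not at hand. A fuller protocol might name the formula.

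**Intention to treat keeps all randomised participants in the analysis.** With about 200 per group, unadjusted power is nominally 70%, and a cross-sectional SD needs only r of about 0.45 for 80%, since √(1 − 200/251.2) = 0.45. This belongs in the range but does not rescue the statement. The section gives 128 as the requirement. Dropouts are retained by carrying values forward or backward, which sets their change to zero and would tend to dilute a real difference, so the nominal figure is optimistic.

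**A journal article condenses.** That would excuse an omitted derivation. Here the article prints a number and a power that its printed inputs do not yield for the comparison between arms.

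**Conclusion.** The point holds in this form: the Statistics section's inputs do not give 128 per group for the between-group comparison, so the stated 80% power does not follow for the primary outcome. The unadjusted requirement is about 252 per group two-sided, or 199 one-sided.

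Baseline-adjusted power cannot be fixed from the document. At the expected 140 per group it runs from 59% to 94%, depending on r and on which SD is meant. Within r = 0.5 to 0.8, only a cross-sectional SD with r of about 0.70 or more supports 80% at 128 per group. The adjusted figures rest on equal variances and on an ANCOVA that includes the baseline value, neither of which is stated. That a within-group formula was used is likely, not shown.

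**What to change.** Rewrite the sample-size paragraph; enrolment need not change.

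- Make the stated power refer to the between-group ANCOVA of VO2max, and say that it adjusts for baseline.
- Say whether 20% is the SD of VO2max or of its change.
- State the formula, the sidedness and the assumed r.
- Report power for a 5% difference, or the difference detectable with 80% power, over r = 0.5 to 0.8 at the expected evaluable number. Give the unadjusted figures for reference (at 140 per group, 55% for a 5% difference, or 80% for 6.7%).
- If 128 came from a within-group formula, say so and do not attach the 80% to the randomised comparison. If it came from ANCOVA with r of about 0.70, state that r and its source.

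The cost is a few sentences and a stated power that will probably look less favourable.

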## Discussion

In RCT studies it is a common strategy to give all participants in the intervention group the same treatment in absolute terms. In studies on physical activity for health promotion the exercises have been cardio-respiratory fitness training at given percentages of VO2max [53,54], strength training at a given percentage of maximum voluntary contraction [17] or fixed combinations [51]. The novelty of this study is that the exercise programs were individually tailored. This may enhance the individuals’ health promotion but at the same time impair the strength of the study in terms of significant effect on the primary outcome. A first attempt in developing IPET was among construction workers [22] where individually tailored exercise programs were developed based on a health check similar to the one in the present study. A combination of cardio-respiratory and strength training for specific body regions was developed for each individual employee and implemented for 12 weeks. A second step was to test intelligent physical exercise adjusted to the work place in terms of possible flexibility in duration, frequency, and supervision in order to fit the IPET to the work tasks [38]. Strength training was performed for 20 weeks but with highly variable training patterns. In the present study, optimizing the duration of the various exercise modes within the 1 hr training once per week during working hours was a challenge and we based our decisions on evidence based exercise training physiology (Table 2). The minimum of training for each of the five categories was 5 min. Further, we considered strength training with large muscle groups also to induce an effect on cardio-respiratory fitness. The last column in Table 2 shows the actual frequencies of the recommended training schedules in the present study. Of the in total 32 potentially possible combinations only 9 combinations were recommended for 12 or more of the participants, i.e. ≥3% of the total number of participants in each of these combinations. Interestingly, these 9 combinations together included more that 85% of all participants. This underlines that such large variety of training schedules as presented in Table 2 may not be needed. Actually, the last column also shows that around 3/4 of employees were recommended neck/shoulder strength training and a similar number cardio training. Both of these training categories were represented in 7 of the above 9 combinations. The particular need for these training activities are not surprising for this workforce, since they are sedentary 8 hrs five days a week and work in constrained neck/shoulder postures. Similarly, it is likely for other occupational groups based on health checks to identify optimal training combinations that are practically manageable at the work site.

### Strengths and limitations

A strength of this study is the rigid RCT design and the involvement of experts within occupational health as well as sports science. However, the enrollment of only approx. 30% of the eligible employees impairs the external validity. Also the randomization on an individual level may have introduced some contamination and cluster randomization could have been superior, but unfortunately not manageable in the present study due to the organization of the enrolled companies.

### Impact of results

The conceptual model presented here is easily applicable for practical use. If proven effective, the intelligent physical exercise training scheduled as well as the information for its practical implementation can provide meaningful scientifically based information for public health policy and health promotion strategies for employees in job groups at high risk for physical inactivity. This knowledge can be beneficial for occupational health professionals, supervisors, companies and employees in these job groups. Because the interventions are carried out during ordinary circumstances at a wide range of Danish workplaces, it is expected that the findings can be transferred and interventions implemented in other workplaces with high physical demands.
